## Abstract

**Introduction:**

Neuropathic pain affects up to 10% of the population and remains difficult to diagnose and treat effectively. Peripheral nociceptor hyperexcitability is thought to drive pain in a substantial subset of patients, yet human studies have not fully defined which nociceptor populations are abnormal or how these abnormalities relate to clinical phenotype, sensory profiling, or genetic mechanisms. Microneurography uniquely enables direct in vivo recording from human C-fibres, offering a mechanistic approach to patient stratification. This observational study investigates the relationships between neuropathic pain, nociceptor excitability, somatosensory phenotype, and genetic variation.

**Methods and analysis:**

We will conduct an observational controlled study at the University of Oxford (2022–2029) following STROBE guidelines. Adults with and without neuropathy or neuropathic pain will undergo deep phenotyping, including questionnaires, neurological examination, quantitative sensory testing, nerve conduction studies, microneurography, skin biopsy, and genetic and transcriptomic analyses. Microneurography recordings will quantify C-fibre axonal properties, excitability, spontaneous activity, and responses to electrical, thermal, and mechanical stimulation. Participants will be stratified by neuropathy grade, neuropathic pain status, somatosensory phenotype, and genetic variants. Primary analyses will compare axonal excitability and related microneurography measures between participants with and without neuropathic pain. Secondary analyses will evaluate the associations between microneurography-derived nociceptor functional profiles and quantitative sensory phenotypes, and will assess the impact of rare ion-channel variants on C-fibre excitability. Multivariable regression, dimensionality reduction, and unsupervised clustering methods will be applied to delineate mechanistically informed patient subgroups.

**Ethics and dissemination:**

Ethical approval was obtained from the South Central – Oxford C Research Ethics Committee (18/SC/0263). All participants will provide informed consent. Findings will be disseminated through peer-reviewed publications, conference presentations, and data-sharing compliant with institutional and funding-body policies.

**Strengths and limitations of this study:**

The study uses microneurography, the only technique that directly records from human nociceptors in vivo, enabling detailed mechanistic assessment of C-fibre function. A deep phenotyping framework, including quantitative sensory testing, skin biopsy, nerve conduction studies, and genetic analysis, allows multidomain integration of clinical, neurophysiological, and molecular data. Classification of C-fibre subtypes using activity-dependent slowing provides a reproducible method to distinguish functional nociceptor populations. Extended microneurography protocols may not be feasible for all participants due to tolerability or signal instability, potentially reducing completeness of some secondary measures. As an observational study, causal inference is limited, and confounding will require careful adjustment despite prespecified statistical analyses.

## Introduction

Neuropathic pain is a type of pain that occurs due to a lesion or disease of the somatosensory system [1]. It is linked to poorer quality of life, increased emotional distress, and higher healthcare utilisation compared to other forms of chronic non-neuropathic pain, such as arthritic pain [2]. Peripheral neuropathy, which is injury to peripheral nerve fibres, is the most common cause. Nearly 10% of the population suffer from peripheral neuropathy [3], with diabetes mellitus the leading cause [4]. In the UK, diabetes prevalence is projected to rise from 6.3% in 2021 to 7.5% by 2045. Diabetic distal symmetrical polyneuropathy affects 30–50% of individuals with diabetes and about half will suffer from chronic neuropathic pain [4]. Rarely, neuropathic pain can result from genetic [5] or immune-mediated changes [6] in ion channel function that leads to peripheral nerve hyperexcitability.

Chronic neuropathic pain remains underdiagnosed, and current treatments offer limited efficacy and tolerability [1]. Experts increasingly advocate mechanism-based treatment approaches [7], yet clinicians still lack robust information to match specific therapies to individual patients [8]. A major reason is the way we currently classify neuropathic pain. Clinicians often base diagnosis on aetiology, even though underlying mechanisms and clinical features can differ within the same aetiology and overlap across different aetiologies. Genetic, biochemical, environmental and psychosocial factors shape the complex pathophysiology of neuropathic pain [4,9–13]. To improve outcomes, we need classification schemes and treatment algorithms that target specific pathophysiological pathways.

Abnormal excitability and activity of peripheral nociceptor fibres appear to drive pain in a subset of people with chronic neuropathic pain [14,15]. Both human and animal studies link neuropathic pain to peripheral neuronal hyperexcitability, and human studies indicate that peripheral nociceptor input can maintain neuropathic pain. For example, topical or systemic lidocaine reduces spontaneous neuropathic pain and mechanical and thermal hypersensitivity in patients with peripheral nerve injury or distal symmetrical polyneuropathy [16]. Pre-clinical models implicate altered expression and gating of voltage-gated sodium channels (NaV) in injured nociceptive fibres as mechanisms for hyperexcitability [14]. Human genetic studies corroborate these findings. For example, rare gain- or loss-of-function mutations in nociceptor channels (e.g., TRPA1, NaV subtypes) cause extreme pain syndromes or insensitivity to pain [5,17]. While variants in the same genes are linked to more common neuropathies such as diabetes and small-fibre neuropathy [10,18]. Investigation of rare genetic variants provides important clues to the molecular mechanisms of neuropathic pain. Measuring nociceptive fibre activity directly can identify those whose pain is driven primarily by peripheral fibre hyperexcitability, thereby uncovering key pathophysiological processes and guiding targeted therapy.

However, human studies have not fully characterised which nociceptor populations are abnormal, how neuronal abnormalities relate to clinical phenotype, or the precise molecular changes involved. Many attempts have stratified patients by clinical and sensory profiles, for example via quantitative sensory testing. [19]. Quantitative sensory testing is a standardised and validated psychophysical tool for the systematic assessment and quantification of an individual's pain perception by applying controlled stimuli to areas of pain [20]. This helps in the objective evaluation of pain conditions and responses. But, these sensory profiles have not been tightly linked to direct measures of nociceptor activity. Surrogate neurophysiological measures such as, large-fibre axonal excitability, do not reliably differentiate painful from painless neuropathies [21]. Direct recordings from nociceptors are therefore essential.

Microneurography is the only neurophysiological tool that records neuronal activity directly from nerve fibres in awake humans [22]. It allows assessment of thin myelinated Aδ and unmyelinated C-fibres (largely composed of nociceptive fibres), which cannot be assessed by conventional nerve conduction studies nor axonal excitability [23]. It is thus ideally suited to investigate peripheral mechanisms underlying neuropathic pain [24,25]. Microneurography studies have shown nociceptor hyperexcitability in pathological states including diabetes and individuals with NaV channel mutations [26–37]. For example, certain NaV1.7 pathogenic variants increase spontaneous activity in previously “silent” nociceptors, whereas other NaV1.8 variants reduce spontaneous firing, demonstrating variant-specific effects across nociceptor subtypes [38–40]. This opens the possibility of personalised, mechanism-targeted treatments.

Nevertheless, it remains unclear how nociceptor populations are affected across different painful neuropathies, how neuronal excitability correlates with clinical and sensory phenotypes, and which molecular mechanisms underlie these changes. This study will investigate these questions.

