**Table pone.0349407.t001:** 

No DSP	No abnormalities on clinical assessment or tests
Subclinical DSP	Abnormal tests but no signs or symptoms
Possible DSP	Symptoms: decreased sensation, positive neuropathic sensory symptoms in the toes, feet, or legs, e.g., numbness, burning; or Signs: symmetric decrease of distal sensation or unequivocally decreased or absent ankle reflexes
Probable DSP	Two or more: neuropathic symptoms, decreased distal sensation, or unequivocally decreased or absent ankle reflexes
Confirmed DSP	Abnormal nerve conduction tests or a measure of small-fibre dysfunction (intraepidermal nerve fibre density or thermal thresholds), and abnormal clinical assessment (a symptom or sign)

Participants are then graded according to the presence or absence of neuropathic pain. Neuropathic pain classification is based on whether the pain present is neuropathic in nature and follows a distinct neuroanatomically plausible distribution.

Participants included in analysis will be divided into groups based on aetiology, neuropathy, and neuropathic pain grading [10].

i. **Diabetic participants** are divided into those with (possible/probable/confirmed) and without a distal symmetrical polyneuropathyii. **Diabetic participants with a distal symmetrical polyneuropathy** are further divided into those with and without neuropathic pain.iii. **Non-diabetic participants** with distal symmetrical polyneuropathy are divided into those with and without neuropathic pain. This will include participants with small-fibre neuropathy, i.e., those participants with injury confined to the small fibres (Aδ and C-fibres.)iv. **Extreme pain phenotypes** include:

**Erythromelalgia** and **paroxysmal extreme pain disorder** – episodic or persistent pain and erythema of the extremities or trunk that is exacerbated by warming and relieved by cooling;

**Familial episodic pain syndrome** – severe episodic pain localised to the trunk and limbs with no structural cause;

**Insensitivity to pain** – inability to feel nociceptive stimuli

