#### Statistical plan.

Analyses will address the relationships between neuropathy, neuropathic pain, quantitative sensory phenotype and microneurography measures of nociceptor excitability and axonal properties. Analyses will be prespecified, scripted for reproducibility and conducted using appropriate statistical software.

Continuous variables will be summarised using mean (standard deviation) or median (interquartile range) depending on distribution; categorical variables will be summarised using counts and percentages. Point estimators will be reported alongside their respective 95% confidence interval. All hypothesis tests will be two-tailed. Where multiple comparisons are performed, p-values will be adjusted using methods appropriate to the comparison (for example Bonferroni or false discovery rate), and this will be reported alongside unadjusted p-values.

The primary hypothesis is that participants with neuropathic pain will exhibit altered axonal properties and excitability compared to those without neuropathic pain. The primary outcome will therefore be a comparison of microneurography measures of axonal excitability and axonal properties between participants with and without neuropathic pain.

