#### Planned primary analysis.

Between-group comparisons (neuropathic pain vs no neuropathic pain) will be conducted using appropriate non-parametric tests (Mann–Whitney U test) where data are not normally distributed, or independent-samples t-tests where normality is satisfied.

Data from individual nociceptive fibres will be analysed with explicit consideration of clustering within participants. Where appropriate, fibre-level measurements will be summarised at the participant level (for example, by averaging) to provide an independent observation per participant for primary analyses. In addition, mixed-effects models will be used, with participant included as a random effect, to account for within-participant variability. Multiplicity arising from multiple outcomes will be addressed using appropriate multiple-comparison adjustments (for example, Bonferroni or false discovery rate correction).

This dual approach allows us to perform conservative primary analyses at the participant level by averaging, while also utilising more sophisticated modelling through a mixed-effects model that retains the detail of the individual fibre data while correcting for the dependence between fibres from the same participant. The mixed-effects model will bridge the participant (unit of inference) and individual fibre (unit of observation) without the statistical error of treating fibres from the same person as independent data points.

Multivariable logistic regression models will be used to examine the association between neuropathic pain status and microneurography-derived measures of axonal excitability and properties, adjusting for prespecified covariates (age, sex, diabetes status, neuropathy severity, and medication use).

Multicollinearity among predictors will be evaluated using variance inflation factors; when two predictors are highly correlated, the variable with greater variance or stronger biological relevance will be retained in the final model.

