#### Sample size justification.

Sample size calculations are based on power to identify differences in QST cluster frequencies and to support clustering and multivariate analyses.

- Using pilot quantitative sensory testing data from DOLORisk, expected cluster frequencies for diabetic distal symmetrical polyneuropathy are 53.9% (sensory loss), 25.0% (mechanical hyperalgesia) and 15.8% (thermal hyperalgesia). For non-diabetic neuropathies the corresponding frequencies are 49.7%, 21.2% and 14.5%.

- For moderate effects (Cohen’s d ~ 0.5) in the quantitative sensory testing cluster analyses, a total of 130 diabetic and 148 non-diabetic participants provides approximately 80% power at α = 0.05.

- For k-means and hierarchical clustering applied after principal component analysis, a conservative estimate requiring 2^8 = 256 participants was used to ensure adequate representation across variable permutations.

- A multivariate regression model with age, sex, diabetes status, neuropathy severity, and medication use will require 8 degrees of freedom to represent all its variables (assuming a categorical variable coding for 4 categories of medication). Allowing for at least 15 event per variable (EPV) we will require a sample size of at least 120 participants for model development. As described above, variable selection and filtering based on multicollinearity will likely increase the EPV.

- Taking these calculations together (and accounting for anticipated success rates in microneurography recordings: minimum 60% for diabetic participants and 80% for non-diabetic participants), the recruitment target is 272 participants (124 diabetic and 148 non-diabetic).

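### The aim asks how different painful neuropathies affect nociceptors, but no planned analysis estimates or compares the pain effect by aetiology, and the primary test pools aetiologies without stratification

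*Protocol article*

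**What the plan says.** The Introduction closes with a list of open questions. The first is that "it remains unclear how nociceptor populations are affected across different painful neuropathies". The commitment follows directly: "This study will investigate these questions".

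Under Data analysis, Patient stratification, the protocol says that "Participants included in analysis will be divided into groups based on aetiology, neuropathy, and neuropathic pain grading". The groups listed include diabetic polyneuropathy with and without pain, non-diabetic polyneuropathy with and without pain, and the extreme pain phenotypes. The Sample size justification keeps the two main aetiologies apart: "the recruitment target is 272 participants (124 diabetic and 148 non-diabetic").

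The Statistical plan sets the primary outcome as a "comparison of microneurography measures of axonal excitability and axonal properties between participants with and without neuropathic pain". Planned primary analysis gives the test: "Between-group comparisons (neuropathic pain vs no neuropathic pain) will be conducted using appropriate non-parametric tests (Mann–Whitney U test"), or a t-test where normality holds. Neither is stratified. The mixed-effects model is described only by its random effect for participant. The same section adds multivariable logistic models of pain status, "adjusting for prespecified covariates (age, sex, diabetes status, neuropathy severity, and medication use").

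The one analysis explicitly stratified by aetiology is the genetic-variant comparison under Secondary analyses.

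**The concern.** Of the Introduction's three open questions, the one on clinical and sensory phenotype is taken up by the first secondary hypothesis and the correlation analyses, and the one on molecular mechanisms by the second secondary hypothesis. The question about different painful neuropathies has no hypothesis and no listed analysis, although the groups needed for it are formed.

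Two things are at stake. First, a pain effect present in only one aetiology would be reported as a feature of neuropathic pain in general, and effects in opposite directions would tend to cancel. Second, the Introduction itself names diabetes among the states with nociceptor hyperexcitability. If the share of participants with pain differs between diabetic and non-diabetic participants, the unadjusted primary test mixes a diabetes difference into the pain difference.

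**Working it through.** **Where each open question is analysed**

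| Open question (Introduction) | Hypothesis | Listed analysis |
|---|---|---|
| Nociceptors across painful neuropathies | none | none by aetiology |
| Excitability against clinical and sensory phenotype | secondary 1 | comparison across sensory clusters; correlations |
| Molecular mechanisms | secondary 2 | variant comparison, stratified by aetiology |

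The protocol gives no power figure for the pain comparison by aetiology, so there is no stated figure to reproduce. The checks below show how a pooled test behaves.

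**Inputs from the protocol.** Recruitment targets are 124 diabetic and 148 non-diabetic, with minimum recording success of 60% and 80%. Evaluable: 124 × 0.60 = 74.4 and 148 × 0.80 = 118.4, taken as 74 and 118 (192 in all).

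**Assumed inputs.** Unit SD within groups, the pain shares, and the size of any diabetes shift. The protocol gives no pain share for the two recruitment groups; its only related figure is that about half of those with diabetic polyneuropathy have chronic neuropathic pain.

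**1. Effect in one aetiology only, equal pain shares.** Half of each stratum in pain; effect 0.6 SD in non-diabetic and 0 in diabetic participants.
- Pooled effect = 0.6 × 118/192 = 0.37 SD.
- By simulation, the pooled t-test is significant in about 70% of runs.

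No imbalance is needed for this. Nothing in the pooled result shows that the effect is absent in diabetic participants.

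**2. Diabetes shift in the unadjusted test, no true pain effect.** Bias = shift × [P(diabetic | pain) − P(diabetic | no pain)].
- Equal shares: the bracket is 0, so there is no bias and type I error does not rise above 5%.
- Shares of 40% diabetic and 65% non-diabetic, shift 0.5 SD:
  - in pain, 74 × 0.40 = 29.6 and 118 × 0.65 = 76.7, total 106.3
  - not in pain, 44.4 and 41.3, total 85.7
  - bracket = 29.6/106.3 − 44.4/85.7 = 0.278 − 0.518 = −0.240
  - bias = 0.5 × (−0.240) = −0.12 SD
  - simulated rejection is about 12% unstratified, against about 5% for a stratum-weighted difference.
- Shares of 30% and 70%, same shift: about 25% unstratified.

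**3. The sign matters.** Take a true pain effect of 0.4 SD in both strata at 40% and 65%.
- Shift +0.5 SD: expected pooled estimate 0.40 − 0.12 = 0.28 SD; power about 46–47% unstratified and 76% stratified.
- Shift −0.5 SD: expected pooled estimate 0.40 + 0.12 = 0.52 SD; unstratified power rises to about 94%, because the bias then inflates the effect.

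**4. Precision of what is missing.** With half in pain, the 95% half-width within a stratum is 1.96 × √(4/n).
- Diabetic: 1.96 × √(4/74) = 0.46 SD.
- Non-diabetic: 1.96 × √(4/118) = 0.36 SD.
- Difference between them: 1.96 × √(4/74 + 4/118) = 0.58 SD.
- Power of the interaction test: about 39% for a 0.5 SD difference in pain effect and 77% for 0.8 SD.

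**The case against.** The strongest reply is that diabetes is already handled. Planned primary analysis includes a logistic model with diabetes status and neuropathy severity as covariates, and Risk of bias and mitigation says confounders will be adjusted for in regression. That stands as far as confounding in that model goes. A reader might infer that the plan lets diabetes distort its pain result throughout; the text does not support this. The exposure is limited to the unadjusted test and depends on unequal pain shares, which are not documented. The rejection rates in step 2 therefore describe that test alone and do not measure the gain over the adjusted model. Adjustment for a main effect does not, however, show whether the pain effect differs by aetiology.

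A second reply is that the Introduction sentence is background, that no hypothesis concerns aetiology, and that pooling suits a study which criticises classification by aetiology. This carries some weight. But the sentence is followed by an explicit commitment, and the claim that mechanisms overlap across aetiologies is itself something a comparison by aetiology would examine.

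A third reply is that a condensed article may leave subgroup estimates to the analysis plan. That is fair for tables and model details. Here, though, the article fixes the primary test as unstratified and does name aetiology strata for the genetic comparison.

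**Conclusion.** The point holds in a limited form. The study commits itself to a question about different painful neuropathies and forms the groups for it, but lists no within-aetiology pain estimate and no pain × aetiology term; its primary test pools the strata. The practical consequence that needs no imbalance is step 1: a 0.6 SD effect in one aetiology only would be read as a general 0.37 SD effect about 70% of the time. The confounding consequence is conditional: zero at equal pain shares, and about 12% type I error under the assumed 40% and 65% shares with a 0.5 SD shift.

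A reader might also infer that the study cannot answer its question. The documents do not support that, because the groups are defined and the data will be collected. The comparison is unplanned and would be imprecise, but it is possible. This is an inexpensive improvement and not a flaw that invalidates the design.

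**What to change.** 1. Stratify the primary comparison of pain with no pain by aetiology (diabetic neuropathy; non-diabetic neuropathy including small-fibre neuropathy). Use a stratum-weighted mean difference, or the van Elteren test in place of the plain Mann–Whitney test.
2. In the mixed-effects model, with the fibre measure as response, add aetiology and a pain × aetiology term.
3. Report the pain difference with its 95% CI within diabetic and within non-diabetic neuropathy, plus the interaction estimate with its CI. Label these as estimation and not as a powered test.
4. State whether diabetic participants without polyneuropathy and the extreme pain phenotypes enter this comparison.

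The change is to analysis wording only; recruitment and data collection run to September 2029, so it can still be prespecified. The cost is wide intervals. The half-widths in step 4 are a best case, since they count all 74 and 118 evaluable participants with half in pain. They widen if diabetic participants without polyneuropathy are left out of the diabetic stratum.
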